**Methods:**

The trial will involve adolescents on the autism spectrum in high school and their parents, who will be alternately assigned to a control group (regular practice) or an intervention group (using the BOOST-A™). The BOOST-A™ was developed using the PRECEDE-PROCEED model, and is based on the self-determination model, and the strengths- and technology-based approaches. It involves participants completing a series of online modules. The primary outcome will be self-determination, because high self-determination has been linked to successful transition to employment among adolescents on the autism spectrum. Secondary outcomes will include domain-specific self-determination, career planning and exploration, quality of life, and environmental support. Data will be obtained from questionnaires completed by the adolescent on the autism spectrum and their parent/s. Data collection will take place at baseline (Time point 1) and 12 months later (Time point 2).

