### Objectives of the trial

The hypothesis for the trial is that the BOOST-A™ will improve self-determination in adolescents on the autism spectrum transitioning to post-school life. The objectives of the trial are to:determine the effectiveness of the BOOST-A™ in improving self-determination in adolescents on the autism spectrum; anddetermine the effectiveness of the BOOST-A™ in improving quality of life; access to environmental supports; career planning and exploration; and vocational exploration among adolescents on the autism spectrum.

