##### Secondary outcome measures

Career planning and exploration will be measured by the Career Development Inventory—Australia (CDI-A) [60]. Career planning and exploration is defined as the ability to explore one’s skills and interests in relation to work, and to seek information related to one’s career to assist in making an informed decision [59]. The first two sections of the CDI-A [60] will be used for this trial as they specifically target career planning and exploration. These two sections contain 18 items and are valid and reliable, independent from the entire CDI-A [60]. The CDI-Australia has been found to have adequate internal consistency (career planning α = .84; career exploration α = .63), concurrent validity (*r* = .6–.8), and construct validity (four factors explaining 44.7% of the variance) [61].

Quality of life will be measured by the Personal Wellbeing Index-School Children (PWI-SC) [62], which is based on the Subjective Wellbeing Homeostasis Theory [63], which asserts that an individual operates to maintain their wellbeing around an average point. The PWI-SC contains seven items; one for each of the seven domains: standard of living, personal health, achievement in life, personal relationships, personal safety, community-connectedness, and future security [62]. The PWI-SC has high internal consistency (α = .82) and construct validity (comparative fit index = .96) [64]. Sensitivity to change was demonstrated in a study that used the PWI-SC as an outcome measure for a youth support program [65].

Environment support will be measured using the Learning Climate Questionnaire (LCQ) [66], which measures an individual’s perception of support from their team, or the environmental aspects that contribute to the development of self-determination. The LCQ consists of 15 items, and has been found to have good construct validity (one factor explaining 63% of the variance) and high internal consistency (α = .96) [66]. The LCQ has been used to evaluate how instructor’s support impacts on students’ learning in college, demonstrating its sensitivity to change [67]. Based on feedback from Pilot A, the LCQ was adapted to meet the needs of adolescents on the autism spectrum and to ensure it was transition planning specific by removing three questions and slightly modifying the language.

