Domain specific self-determination was measured by the Transition Planning Objectives Scale (TPOS). The TPOS was designed specifically for this trial, because the authors could not identify an existing standardized tool that comprehensively evaluated the transition planning objectives identified in the needs assessment (Fig. 1). The primary researcher (MH) developed the scale based on the transition planning objectives and the measure of processes of care (MPOC) [68]. The MPOC was designed to assess parents’ perceptions of the care provided to their children by health professions in rehabilitation centers. Its underlying concepts align with those of the transition planning objectives, including enabling partnerships and family-centered care. The TPOS consists of 16 items, each of which addresses an objective in Fig. 1. Each item is rated on a 10-point Likert scale, anchored by strongly disagree to strongly agree. The measure was reviewed by the research team and then piloted with six adolescents on the autism spectrum and their parents, after which minor modifications were made. Since the validity and reliability of the transition planning objectives scale is not yet known, the data obtained from this measure will be interpreted and reported with caution. In addition, it is recommended that future studies aim to validate this outcome measure.

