##### Statistical analysis

Simple descriptive statistics (frequencies and percentages for categorical variables; means, standard deviations, ranges for continuous variables) will be used to summarize the demographic and baseline profiles of participants. These baseline variables will include the assessment of autism severity (using the SRS-2), and the outcome measures described above. The Chi square or *t* test (as appropriate) will be used to compare the profiles of participants between the intervention and control groups. If any continuous data are found to be not normally distributed (from the Kolmogorov–Smirnov test), these data may either be transformed to improve their normality or analyzed using an appropriate non-parametric test.

Effectiveness of the intervention for the AIR, the primary outcome, will be determined by calculating the change from Time point 1 to Time point 2, and comparing the changes within and between intervention and control groups using dependent and independent *t* tests (or non-parametric Wilcoxon signed rank tests and Mann–Whitney U test if the data are not normally distributed). If the analysis reveals differences in baseline characteristics between the intervention and control groups, the analyses will be adjusted for these differences using a general linear model (GLM). Analysis of secondary outcomes will be performed using a multivariate ANOVA (MANOVA). Analyses will be performed using an intention-to-treat strategy, where participants will be classified as belonging to the group (intervention or control) to which they were initially allocated, regardless of the treatment they actually received. Participants who do not provide outcome data at Time point 2 will still be included in the trial, and their Time point 1 data will be used for Time point 2 to allow for intention-to-treat analysis of the data. The Statistical Package for the Social Sciences (SPSS v.22) will be used to analyze the data, and a p value of .05 will be used as the level of statistical significance in all inferential analyses.

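### A single MANOVA for the secondary outcomes cannot answer the separately named outcomes of objective 2, and as written it includes the unvalidated TPOS, which could make it significant alone

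*Protocol article*

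**What the plan says.** The Statistical analysis section of the protocol article gives the secondary outcomes one sentence: "Analysis of secondary outcomes will be performed using a multivariate ANOVA (MANOVA"). It adds that "a p value of .05 will be used as the level of statistical significance in all inferential analyses". It describes no follow-up tests, order of testing or multiplicity adjustment for these outcomes.

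The abstract lists the set: "Secondary outcomes will include domain-specific self-determination, career planning and exploration, quality of life, and environmental support". The instruments are the TPOS, CDI-A, PWI-SC and LCQ respectively. The article does not say whether the two CDI-A sections enter as one score or two, but it reports their reliabilities separately ("career planning α = .84; career exploration α = .63").

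The second objective, under Objectives of the trial, is to determine effectiveness in "improving quality of life; access to environmental supports; career planning and exploration; and vocational exploration among adolescents on the autism spectrum". Domain-specific self-determination, which the TPOS measures, is not in that list.

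On the TPOS, the Secondary outcome measures section says that "the validity and reliability of the transition planning objectives scale is not yet known" and that "the data obtained from this measure will be interpreted and reported with caution". It also says that each of the 16 items corresponds to one of the Fig. 1 transition planning objectives. The Outcome measures section says the program was developed from those objectives. Nothing in the article keeps the TPOS out of the MANOVA.

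**The concern.** The stated method and the stated objective do not match. Objective 2 asks whether quality of life, environmental support and career planning and exploration each improve. A significant MANOVA says only that the arms differ on some combination of scores, and gives neither the score, the size of the difference nor a confidence interval.

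The TPOS makes this more serious. It follows the program's content closely and has unknown measurement properties, so a difference on it is the hardest to interpret. The promised caution governs how TPOS results are reported. It does not remove the TPOS from the joint test, and its contribution cannot be subtracted from the joint p value afterwards.

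The risk is that a TPOS-driven result is read as success on objective 2. The Ethics, consent and permissions section makes the later offer of the program to controls depend on its being shown to achieve the trial objectives, so that reading would have a practical consequence.

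**Working it through.** **The plan's own figure.** The article gives no figure for the secondary analysis. Its one sizing figure is 40 per group for a standardized difference of 0.6, 80% power and alpha .05. The two-sided formula 2(1.960 + 0.842)²/0.6² gives 43.6, so 44 per arm; power at 40 per arm is about 76%. A nomogram is read by eye and the sizing is a separate matter, so 40 per arm is taken as given below.

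**Inputs.** From the article: n = 40 per arm, 1:1 allocation, alpha .05 (two-sided assumed). Assumed: p = 4 scores (one per instrument) or p = 5 (CDI-A sections scored separately); a common correlation ρ of 0 to 0.5 between scores; a true difference d on the TPOS only.

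**Step 1: can the TPOS alone make the MANOVA significant?** With two groups, MANOVA is Hotelling's T². Its F statistic has p and 2n − p − 1 degrees of freedom (75 for p = 4, 74 for p = 5) and noncentrality

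λ = (n/2) · d² · m, where m = [1 + (p − 2)ρ] / {(1 − ρ)[1 + (p − 1)ρ]}.

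For d = 0.6 the first part is 20 × 0.36 = 7.2; for d = 0.8 it is 20 × 0.64 = 12.8.

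| p | ρ | m | λ, d = 0.6 | P(significant) | λ, d = 0.8 | P(significant) |
|---|---|---|---|---|---|---|
| 4 | 0 | 1.00 | 7.2 | 52% | 12.8 | 80% |
| 4 | 0.3 | 1.20 | 8.7 | 61% | 15.4 | 88% |
| 4 | 0.5 | 1.60 | 11.5 | 75% | 20.5 | 96% |
| 5 | 0 | 1.00 | 7.2 | 48% | 12.8 | 76% |
| 5 | 0.3 | 1.23 | 8.9 | 58% | 15.8 | 86% |
| 5 | 0.5 | 1.67 | 12.0 | 73% | 21.3 | 95% |

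Correlation with scales that do not move raises the probability, because those scales then act as covariates for the TPOS.

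**Step 2: what if scale-level t tests at .05 follow a significant MANOVA?** The article does not say that they do, so this step is conditional. It was simulated with 40,000 trials per setting.

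- No scale differs: at least one false positive after a significant MANOVA in 3.8–4.8% of trials. Here the gate works.
- Only the TPOS differs (d = 0.6 to 1.2): at least one false positive on another scale in 11.6–14.4% of trials with p = 4 and 14.1–18.4% with p = 5.

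As a check, once the TPOS effect is large enough that the gate nearly always opens, independent scores should give 1 − 0.95³ = 14.3% for three other scores and 1 − 0.95⁴ = 18.5% for four. The simulation reaches 14.4% and 18.4% at ρ = 0.

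**Step 3: comparator.** Holm across all the scores kept the chance of any false positive on scales with no effect at about 4–5% in every setting.

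School clustering and carried-forward baseline values were not modelled.

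**The case against.** The strongest reply is that the article describes no scale-level tests. It is a condensed account, and the procedure after an omnibus test is commonly left to an analysis plan. A reader might infer that the plan tests the other scales without error control; the text does not support that. No such tests are stated, and a MANOVA gate does control error when nothing differs. The 12–18% range is therefore conditional, and 18.5% is only the ceiling for five independent scores. The flat .05 is a significance level for each analysis, not a promised family-wise rate.

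Two further inferences also fail. One is that the MANOVA discards participants with missing outcomes: the Statistical analysis section carries Time point 1 data forward for those without Time point 2 data. The other is that there is no baseline adjustment: the sentence just before the MANOVA sentence adjusts the analyses by a general linear model if baseline characteristics differ, and it may extend to the secondary outcomes.

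It is also fair to say that all the outcome measures were chosen with the transition planning objectives in mind, that the LCQ was itself adapted, and that a larger movement on the TPOS is a prediction. The article is open about the TPOS's status. School clustering affects the primary t tests as much as the MANOVA.

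What remains is the stated method itself. If no scale-level analysis follows, objective 2 is not answered outcome by outcome. If one does follow, the MANOVA gives it only weak protection. In both cases the TPOS is in the joint test.

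**Conclusion.** The point holds in this limited form. The mismatch between one omnibus test and the separately named outcomes of objective 2 follows from the text and needs no assumption. So, on the natural reading, does the presence of the TPOS in that test.

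The size is conditional. With 40 per arm, four or five scores and correlations of 0 to 0.5, a TPOS-only difference makes the MANOVA significant in about 48–75% of trials at d = 0.6 and 76–96% at d = 0.8. If unadjusted tests at .05 follow, the chance of a false positive on another scale is then about 12–14% (four scores) or 14–18% (five). The TPOS effect, the correlations and the number of scores are assumptions.

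The primary analysis of the AIR is not affected by this point.

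**What to change.** Replace the MANOVA sentence with one between-group model for each CDI-A, PWI-SC and LCQ score, adjusted for that score's baseline value and allowing for clustering by school, since students at the same school are placed in the same arm. Report each between-group difference with a 95% CI. State whether the CDI-A gives one score or two. Report the TPOS separately as exploratory, in line with the caution already promised.

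Then choose one of two ways to handle the per-outcome p values and say which: label them unadjusted and supportive, or apply Holm across the CDI-A, PWI-SC and LCQ scores. This is a matter of choice for secondary outcomes. Holm's cost is a stricter threshold per outcome: the smallest p value must reach .05/3 = .0167 with three scores or .05/4 = .0125 with four.

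The change is to analysis wording only and needs no new data. It should be fixed before outcome data are compared by group.

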### Trial design and procedures

A controlled clinical trial [47] will be used to determine the effectiveness of the BOOST-A™ in improving the self-determination of adolescents on the autism spectrum; and in improving their outcomes of quality of life, access to environmental supports, and career planning skills. The trial will be a cluster group, two-arm, superiority trial with 1:1 allocation ratio. The trial will aim to detect any difference in these outcomes between participants in the intervention group (BOOST-A™) and a control group. Figure 2 shows the schedule of enrolment, intervention, and assessment for the trial. Participants in the intervention group will complete the BOOST-A™ at home and/or at school. Participants will complete the BOOST-A™ over a period of 12 months. This timeframe was chosen to ensure the participants have adequate time to complete all four modules, including the initial team meeting and at least one review meeting. Adherence will be monitored via website analytics, including number of modules completed and number of logins to the BOOST-A™ website. Participants allocated to the control group will participate in the existing post-school planning process used at their school (regular practice).

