##### Sample size

Altman’s nomogram equation was used to determine the sample size. A total sample of n = 80 (n = 40 in each group) would be the minimum required to identify a standardized difference of 0.6 (i.e., Cohen’s *d*) [53], with a power of 80% and a critical alpha value of .05.

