#### Data collection

Outcome data will be collected via an online survey using Qualtrics software (Version 2016). The survey containing the outcome measures for the trial will be emailed to participants at two data collection points: at baseline (Time point 1), and 12 months later (Time point 2). Participants will complete the online survey in their own environments, which could be home, work, or school. Demographic information will be collected from parents at Time point 1. This information will include the adolescent’s age, gender, year level at school, and their residential postcode (to determine socioeconomic status). It is anticipated that completing the online outcome measures will take 30–45 min each time. Participants will be given a leeway of two months after each scheduled data collection point to complete the outcome measures. Participants will be reminded, as needed, by the primary researcher via telephone and email to complete the outcome measures. The trial commenced on 26 November 2015 (Time Point 1), and data collection for the post-measures began on the 26 November 2016 (Time Point 2).

The Social Responsiveness Scale-Second Edition (SRS-2) [48] will be used to classify autism severity. Parents will complete the School Age Rating Form, which is designed for children aged 4–18 years. The SRS-2 consists of 65 items and can be administered in 15–20 min. The scale results in a total score and a *t*-*score*, which can be used as an index of severity of social deficits on the autism spectrum. Scores can be interpreted as falling into one of the following four categories: within normal limits, mild deficit, moderate deficit, and severe deficit. The scale has been standardized using a nationally representative sample, and has strong psychometric properties including high internal consistency (α = .95); construct validity (two strong factors); test–retest reliability (*r* = .88–.98); and interrater reliability (*r* = .91 between mothers and fathers) [48]. Studies have shown that the SRS-2 can detect clinically meaningful and statistically significant differences between typically developing children and those diagnosed with autism [54]. Additional independent variables for this trial will be comorbidities (including mental health), gender, age, and socioeconomic status.

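### Baseline carried forward is the only stated rule for missing 12-month outcomes; it sets each non-responder's change to zero, can bias the effect either way, and is not reliably conservative

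*Protocol article*

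**What the plan says.** The Statistical analysis section of the Protocol article says that effectiveness on the AIR "will be determined by calculating the change from Time point 1 to Time point 2", with the changes compared within and between arms by t tests or their rank-based counterparts. On missing data it says "Participants who do not provide outcome data at Time point 2 will still be included in the trial", and then that "their Time point 1 data will be used for Time point 2 to allow for intention-to-treat analysis of the data". The sentence before these defines intention to treat as classification by the group first allocated, whatever treatment was received.

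The Data collection section schedules the outcome survey twice, at baseline and at 12 months, so baseline is the only value that can be carried forward. The article states no other method for missing outcomes, no sensitivity analysis and no expected loss. The Sample size section gives 40 per group as the "minimum required to identify a standardized difference of 0.6" and mentions no loss. That matters here only because the size of the problem then has to be worked out from assumed rates.

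**The concern.** The rule is fixed in the text, so it is not a detail left to a fuller document. It gives every non-responder a change of zero with no uncertainty, and the article offers no reason why zero should be right. Some of its content points the other way:

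- Controls receive their school's existing planning process (Trial design and procedures), and the Background links transition planning to better self-determination. Change in both arms is therefore credible, though not documented.
- The test–retest correlation quoted for the AIR is .74 over three months (Primary outcome measure). If the variances on the two occasions are equal, the SD of change is √(2 × (1 − 0.74)) = 0.72 score SDs. Individual changes with no spread at all do not fit that figure.

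The stated purpose does not justify the rule either. Keeping participants in their allocated arm says how they are classified, not what value they would have reported.

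At stake is the primary estimate. It would depend partly on how many participants fail to return the second survey in each arm, and on how far adolescents change over a year whatever their treatment.

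**Working it through.** **The plan's own figure.** For d = 0.6, 80% power and two-sided α = .05, n per arm = 2 × (1.960 + 0.842)² / 0.6² ≈ 43.6, so 44 per arm (88 in total), or 45 per arm with the t distribution. A one-sided test needs 35 per arm. The stated 40 per arm gives 76.5% two-sided power. The stated 80 is probably an approximate nomogram reading. Nothing below depends on this.

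**Inputs.** From the article: 40 per arm, 1:1 allocation, standardized difference 0.6, α = .05. Assumed: the 0.6 applies to the change score, whose SD is set to 1; testing is two-sided; loss is 0–40% per arm; non-response is unrelated to outcome within arm; natural change is as stated in each case.

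**Formulas.** With mean change μ and loss d in an arm, baseline carried forward gives
- expected arm mean: (1 − d)μ
- variance of change: (1 − d) + d(1 − d)μ²
- bias of the treatment effect: −d_I μ_I + d_C μ_C (I = intervention, C = control)

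**Equal loss.** The effect becomes (1 − d) × 0.6. At 20% this is 0.8 × 0.6 = 0.48.

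**Unequal loss, true effect 0.6.** With 30% v 10% loss and a 0.2 SD natural gain, 0.7 × 0.8 − 0.9 × 0.2 = 0.56 − 0.18 = 0.38, which is 37% too small. The variances are 0.834 and 0.904, so the SE is √((0.834 + 0.904)/40) = 0.208 and power is about 44%. Observed outcomes alone (28 v 36) give an SE of √(1/28 + 1/36) = 0.252 and power of about 65%.

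**Unequal loss, no true effect.** With 30% v 10% loss and a 0.3 SD natural gain, 0.7 × 0.3 − 0.9 × 0.3 = −0.06. If scores fall by 0.3 SD instead, the bias is +0.06 and favours the arm with more loss.

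**Standard error.** Simulation (20,000 trials per row, 40 per arm, true effect 0.6, no change in controls):

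| Loss in each arm | Mean estimate | Mean SE, carried forward | Mean SE, observed only | 95% CI coverage of 0.6, carried forward |
|---|---|---|---|---|
| 0% | 0.60 | 0.223 | 0.223 | 95% |
| 10% | 0.54 | 0.213 | 0.235 | 94% |
| 20% | 0.48 | 0.203 | 0.250 | 91% |
| 30% | 0.42 | 0.191 | 0.268 | 84% |

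As data are lost the SE falls, below even its complete-data value. The drop in coverage reflects both the shifted estimate and the small SE.

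**Type I error.** With no effect and 20% loss in each arm it is about 5%, whether natural change is 0 or 0.3 SD. With a 0.5 SD gain in both arms it is 7.7% at 30% v 10% loss (bias −0.10) and 12.1% at 40% v 10% (bias −0.15).

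**The case against.** **The bias is conditional.** A reader might infer that the rule must bias the result, or must produce false positives. The documents do not support that. The bias depends on loss by arm and on the true change of non-responders, and neither is given. It can cancel: true changes of 0.9 and 0.3 with 10% and 30% loss give 0.81 − 0.21 = 0.60. With equal loss, a real effect is diluted and a null effect stays null.

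**Unequal loss is plausible, not shown.** Only the intervention arm has modules and team meetings to complete. Yet both arms receive the same survey, a two-month leeway and reminders.

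**The variance claim is limited.** A reader might infer that the t test misstates the variability of its own estimate. It does not: at 20% loss the mean SE is 0.203 and the estimator's sampling SD is 0.204. The SE is too small only as a measure of uncertainty about the true 12-month effect.

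**A missing-at-random method can do worse.** This is the strongest objection. Suppose intervention non-responders are non-users with only the natural change. With 30% v 10% loss, a 0.2 SD gain and a 0.6 SD effect in responders, the true effect by allocation is (0.7 × 0.8 + 0.3 × 0.2) − 0.2 = 0.42. Carrying baseline forward gives 0.38, an error of −0.04. Observed outcomes give 0.60, an error of +0.18, and missing-at-random methods that condition only on baseline would be close to that. This stands. It does not justify zero change as the sole rule, but it does mean that the replacement needs a sensitivity analysis covering this case.

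**The normality check.** A block of exact zeros might also affect the test that chooses between t and rank methods. No calculation supports this, so no weight is placed on it.

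**Conclusion.** The concern holds in a conditional form. It is certain that every non-responder receives an AIR change of exactly zero, that this is the only stated rule, and that intention to treat does not call for it. The rule cannot be defended as conservative. With equal loss d and non-response unrelated to outcome, it multiplies the effect by (1 − d). With unequal loss and general change over the year, it can err in either direction.

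The sizes (0.48 or 0.38 instead of 0.60, and about 0.06 SD under no effect) rest on assumed loss and natural change. Confidence is therefore high for the mechanism and low for the magnitude in this trial. Because the rule governs the primary conclusion and can be replaced using data already being collected, it should be changed.

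**What to change.** Before outcomes are compared by arm, replace the rule as the primary method with one of these:

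- a likelihood-based model of both time points (arm by time, baseline covariates) for all consented participants in their allocated arm, allowing for clustering by school; or
- multiple imputation by arm using baseline AIR, SRS-2, age, gender and socioeconomic status, followed by the baseline-adjusted comparison, also allowing for school.

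The population is put as consented participants because the Treatment allocation section allocates before consent, so some of those allocated may have no data. School is needed because the same section places schoolmates in one arm.

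Add a delta-adjusted sensitivity analysis for data missing not at random, including the case in which intervention non-responders have only control-like change. Keep baseline carried forward solely as a labelled sensitivity analysis. Report the number missing in each arm.

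The cost is a modest amount of analysis work and reliance on a missing-at-random assumption, which the sensitivity analysis tests. No new data are needed. Since the Data collection section dates the start of the 12-month survey to 26 November 2016, the change should be dated and recorded as made before any comparison by arm.
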